## Outcome measures

### Primary outcome

Number of pregnancies, miscarriages, and live births in women with TS following autotransplantation of cryopreserved and thawed ovarian cortical tissue, in relation to karyotype, age, prior hormonal status, and imaging findings.

### Secondary outcomes

Primordial follicle density (number/mm³) in relation to karyotype, age, hormonal status, and imaging findings.Identification of markers and predictors of POI in girls with TS < 18 years following OTC.Epigenetic age acceleration before and after POI based on DNA methylation patterns in leukocytes.Association between DNA methylation, RNA expression and POI in leukocytes and ovarian tissue.Global gene expression and proteomic profiles in oocytes and granulosa cells from follicular fluid of small antral follicles.In vitro maturation potential and karyotype of oocytes from small antral follicles.TGF-beta signaling and steroidogenesis in theca cells, granulosa cells, and follicular fluid from small antral follicles.The effect of unilateral oophorectomy for OTC on residual ovarian function and pubertal development in girls with TS.

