**Methods:**

The Danish Turner Syndrome Cryopreservation Study is a nationwide, prospective cohort study with long-term follow-up, combining observational and interventional elements. Girls with TS aged 2–17 years are invited to participate. As ovarian reserve is depleted before adulthood in most girls with TS, all participants undergo ovarian function assessment to evaluate the likelihood of remaining viable follicles. If follicles are deemed present, unilateral OTC may be offered. The primary outcome is the number of pregnancies, miscarriages, and live births following autotransplantation of cryopreserved and thawed ovarian tissue in adulthood. Secondary objectives include identifying early predictors of POI, assessing the impact of oophorectomy on ovarian function and pubertal progression, and exploring molecular mechanisms of ovarian dysgenesis through genetic and epigenetic analyses of ovarian and peripheral tissues. Recruitment began in January 2024 and is ongoing at three university hospitals across Denmark. Follow-up is expected to continue until 2050.

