While TS is associated with multiple health challenges, infertility remains one of the most emotionally distressing, with the inability to have a genetically related child representing a major source of grief [15]. Ovarian tissue cryopreservation (OTC) presents a unique opportunity to preserve fertility in girls with TS before the complete depletion of germ cells. In contrast to oocyte vitrification, which requires post-pubertal maturation, OTC can be performed regardless of pubertal status, making it feasible even in infancy and early childhood. While OTC has proven successful in pediatric cancer patients treated with gonadotoxic therapy [16], its use in girls with TS remains experimental. Only a few TS cohorts have undergone OTC in Sweden [14, 17], the Netherlands [18], Denmark, the United Kingdom, and Australia [19]. Reports of subsequent autotransplantation are extremely limited, with only three documented cases in females with TS [17, 20]. Of these, only one reported a subsequent pregnancy, which unfortunately ended in an early miscarriage.

The Danish Turner syndrome Cryopreservation Study is a prospective cohort study designed to evaluate the long-term reproductive outcomes following OTC in childhood and subsequent autotransplantation in adulthood in women with TS. The study will also explore the natural history of TS, with particular focus on the progression of premature ovarian insufficiency (POI) and early predictors of POI during childhood. Furthermore, both genetic and epigenetic mechanisms underlying germ cell depletion will be investigated by integrating analyses of DNA methylation, gene expression, and proteomic profiles in ovarian and peripheral tissues.

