### Assessment of ovarian function

Since ovarian reserve is depleted before adulthood in most girls with TS, all participants undergo ovarian function assessment to evaluate the likelihood of remaining viable follicles. This approach aims to avoid unnecessary surgery and ensures that outcomes following OTC reflect the subgroup of girls with remaining viable follicles – and to whom OTC and later autotransplantation may be a feasible fertility preservation strategy.

Ovarian function is assessed through repeated measurements of serum hormone levels (including anti-Müllerian hormone (AMH), Inhibin B, gonadotropins (follicle stimulating hormone (FSH) and luteinizing hormone (LH)), and estradiol (E2)), clinical features of TS (such as pubertal development and current need for hormone replacement therapy), and imaging of the uterus and ovaries using transabdominal ultrasound (TAUS) and/or magnetic resonance imaging (MRI).

*Sufficient ovarian function for OTC was predefined as follows:*

In prepubertal girls: age-adjusted AMH >-2 SD or FSH < + 2 SD, along with antral follicle count (AFC) >10th percentile on TAUS or MRI [13, 22, 23].In peri-/postpubertal girls: spontaneous pubertal development >-2 SD according to puberty nomograms [24], AMH, E2, and inhibin B >-2 SD, FSH and LH < + 2 SD, along with AFC >10th percentile on TAUS or MRI [13, 22, 23].

*Insufficient ovarian function for OTC was predefined as follows:*

In prepubertal girls: AMH < -2 SD and FSH >+ 2 SD, along with streak ovaries or AFC < 10th percentile on TAUS or MRI [13, 22, 23].In peri-/postpubertal girls: absent or arrested pubertal development [24], primary or secondary amenorrhea, AMH, E2, and inhibin B < -2 SD, FSH >+ 2 SD, along with streak ovaries or AFC < 10th percentile on TAUS or MRI [13, 22, 23].

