Following ovarian function assessment, the girls and their parents will discuss the results with both a gynecologist and a (pediatric or adult) endocrinologist with expertise in TS-related fertility. During this consultation, they will be informed about whether OTC can be offered, associated surgical risks, success rates of OTC in other patient groups, previous experiences with OTC in girls with TS, the risks associated with pregnancy, and alternative options for parenthood. They will also be informed about the increased risk of chromosomal abnormalities in potential children, and in the event of a pregnancy, the woman will be offered prenatal diagnostics (chorionic villus sampling). In cases where clinical, biochemical, and imaging findings do not provide a clear-cut assessment, cryopreservation may be considered following expert clinical assessment and a collaborative decision-making process with the family and the endocrinologist and/or gynecologist.

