
The Danish Turner Syndrome Cryopreservation Study represents an important step toward understanding the potential and limitations of OTC in TS. By prospectively following girls with TS across the full spectrum of ovarian function – including those not deemed eligible for OTC – the study will provide valuable insights into the progression of ovarian insufficiency, as well as long-term reproductive outcomes following OTC and subsequent autotransplantation. These findings will help refine patient selection, enhance clinical counselling, and support evidence-based decision-making regarding fertility preservation in this population.

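### The only outcome naming predictors of POI is limited to girls after OTC, which does not match the stated objective of natural history and early predictors in childhood

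*Protocol article*

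**What the plan says.** The objective is stated without any restriction to operated girls. The abstract (Methods) reads: "Secondary objectives include identifying early predictors of POI, assessing the impact of oophorectomy on ovarian function and pubertal progression". Predictors of POI and the impact of oophorectomy are thus two separate items. The Background describes an exploration of natural history "with particular focus on the progression of premature ovarian insufficiency (POI) and early predictors of POI during childhood". The Discussion says what the cohort offers for this purpose: "By prospectively following girls with TS across the full spectrum of ovarian function – including those not deemed eligible for OTC".

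The list under Secondary outcomes gives a narrower population: "Identification of markers and predictors of POI in girls with TS < 18 years following OTC". The effect of unilateral oophorectomy on residual ovarian function and puberty is a separate entry in the same list.

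Selection for OTC is described under Assessment of ovarian function. For prepubertal girls the criterion is "age-adjusted AMH >-2 SD or FSH < + 2 SD, along with antral follicle count (AFC) >10th percentile on TAUS or MRI". For peri- and postpubertal girls it is spontaneous pubertal development within range plus "AMH, E2, and inhibin B >-2 SD, FSH and LH < + 2 SD, along with AFC >10th percentile on TAUS or MRI". Where the findings are unclear, "cryopreservation may be considered following expert clinical assessment and a collaborative decision-making process". The section on OTC states that one ovary is removed by laparoscopy.

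**The concern.** The objective and the outcome name different populations. A predictor analysis meant to describe natural history needs girls whose ovaries are left alone, over as wide a marker range as the at-risk cohort provides. The outcome as written uses girls who have had an ovary removed and who were mostly offered surgery because their markers looked favourable.

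Three things are at stake. Unoperated girls still at risk of POI drop out of the analysis, although the Discussion says that girls not deemed eligible for OTC are followed to learn about progression. The range of several candidate predictors is narrowed, which tends to weaken their apparent association with POI. And any effect of surgery on POI becomes part of the outcome being predicted. A family deciding before surgery needs to know the expected course without OTC as well as after it, and this outcome would inform only the second.

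**Working it through.** The plan gives no figure on this point. Its one calculation (72 patients, for the live birth rate) is unaffected. The check is a comparison of the sections.

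1. **Objective against outcome.** The abstract and Background ask for early predictors of POI in childhood, with no OTC condition. The Discussion includes girls not deemed eligible for OTC. The outcome list requires that OTC has taken place. No other listed outcome covers hormonal, imaging or karyotype predictors of POI. Two entries concern POI without an OTC limit (epigenetic age before and after POI, and methylation and RNA expression in relation to POI, both in leukocytes), but these are molecular questions.

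2. **Overlap between selection criteria and candidate predictors.** Taking the predefined rule for sufficient function:
   - Prepubertal: (AMH above −2 SD **or** FSH below +2 SD) **and** AFC above the 10th percentile. A girl with AMH below −2 SD can still qualify through FSH, so AMH is not cut off at −2 SD here. Inhibin B, E2 and LH are not thresholds in this group.
   - Peri-/postpubertal: pubertal progress, AMH, E2, inhibin B, FSH, LH **and** AFC must all be in range.
   - Unclear cases: OTC remains possible after expert assessment.
   - Karyotype, mosaicism and methylation: not thresholds in either group.

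   The low-function end is therefore thinned, more in older girls than in younger ones, but not removed. The Discussion itself links low AMH to imminent POI, so AMH is plainly a candidate predictor.

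3. **Effect of the procedure.** The Discussion concedes that taking out one ovary early could speed up loss of a reserve that is already poor. It also says that general-population findings on the age of menopause may not carry over to these girls. In the earlier follow-up study it cites, AMH fell in most girls in the first year after OTC and then levelled off or rose, sometimes above the starting value. The direction and size of any effect on POI are thus open, and a post-OTC group alone cannot separate that effect from natural course.

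4. **Who is left out.** The informative natural-history group is girls without POI at baseline who do not have OTC, together with time at risk before OTC in those who later have it. The article enrols and assesses such girls, but the outcome's wording excludes them.

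**The case against.** The strongest reply is that the objective does not rest on one line. The study has four arms defined by ovarian reserve and by function after ovary removal, all participants have repeated hormone measurements, and ineligible girls are followed. Follow-up by arm is in Figure 1, which is not visible here, and the full protocol is not shown. This stands to the extent that the defect is one of outcome definition, not of data collection. A reader might infer that the study cannot deliver its natural-history objective; the document does not support that.

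Second, prognosis after OTC is a legitimate question, and a girl considering surgery needs it. That also stands, and is a reason to keep it as a separate outcome. It does not make it the objective in the abstract and Background, where the impact of oophorectomy is listed apart from predictors.

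Third, a reader might take the outcome to use markers measured after OTC. The wording does not say so: the phrase may describe the girls, and pre-OTC markers are collected in everyone.

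Fourth, a reader might wish to put a number on the loss from range restriction. It can be illustrated only with inputs the document does not give. Assume AMH SD scores in the cohort are normal with mean −3 to −1 and SD 1.5, the log-odds of POI fall by 0.8 or 1.2 per SD score, and selection is a clean cut at AMH above −2 SD. The AUC of AMH for POI then falls from 0.77–0.85 in the whole cohort to 0.64–0.77 in the selected girls. This is not an estimate for the study: the real rule is not a single cut on AMH, and the comparator includes girls who already have POI at baseline, whom a proper analysis would also exclude.

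**Conclusion.** The mismatch is real and can be read directly from the text. The population of the only outcome naming markers and predictors of POI is narrower than the objective it should serve, and differs from it in two ways that matter: selection largely on candidate predictors, and loss of an ovary. The direction of the first (a narrower marker range) follows from the eligibility rule. The second is a possibility that the article itself raises, not an established effect. The size of either cannot be derived from the document.

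The point concerns one secondary outcome. The primary outcome, the sample size and the offer of OTC are untouched. It is worth correcting while recruitment is ongoing, because otherwise the natural-history analysis would need a later change of population or would be reported outside the listed outcomes.

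**What to change.** Restate the outcome along these lines: *predictors of POI before age 18 in all enrolled girls without POI at baseline, using markers measured at baseline (before any OTC)*. Show girls with and without OTC separately as a main analysis, for example by splitting each girl's follow-up at OTC so that time before surgery counts as unoperated.

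A pooled model with OTC as a time-dependent term can be added as support. It should not carry the conclusion: OTC is offered on the same markers, so the term is confounded by indication and operated and unoperated girls overlap only partly. For the same reason, leaving the unoperated group at OTC depends on the markers, and the report should say so.

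Keep POI after OTC as a distinct outcome under its own heading.

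The cost is the rewording of one outcome, the addition of another and a somewhat more complex analysis. The article already describes baseline assessment of all participants and follow-up of girls not eligible for OTC, so it suggests no need for a new arm. The number of unoperated girls still at risk is not stated, and precision in that group may be low.

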### Tertiary outcomes

Uterine growth after OTC in girls with TS < 18 years not receiving HRT.The presence of somatic mosaicism, including differences in karyotype between buccal cells and peripheral lymphocytes, as well as the presence of germline mosaicism.Complications related to laparoscopic unilateral oophorectomy in girls with TS < 18 years.Bone mineral density, bone microarchitecture, and body composition before and after OTC.Quality of life in relation to ovarian function and OTC.Effect of endogenous estrogen on bone metabolism and cardiovascular risk markers after autotransplantation of cryopreserved and thawed ovarian cortical tissue.

## Statistical considerations and data analysis

All project data are entered into a centralized pseudo-anonymized REDCap database [29, 30], registered in the internal records of research projects maintained by the Central Denmark Region.

### Sample size calculation

Given the exploratory nature of this study, the live birth rate following OTC in women with TS is unknown. Power calculations are therefore based on data from female cancer survivors treated with gonadotoxic therapy. In this group, pregnancy rates following transplantation of thawed ovarian cortical tissue are approximately 50% and live birth rates around 35% [26, 31–33]. Spontaneous miscarriage occurs in an estimated 30–45% of TS pregnancies with autologous oocytes [11, 34]. Based on these figures, approximately seven patients would require OTC for one live birth to occur. Using the formula from Hulley et al. [35] for dichotomous outcomes (expected LBR of 0.25; a confidence interval width of 0.2; and a significance level (α) of 0.025) the required sample size is 72, corresponding to 18 expected live births. We aim to include 100 girls undergoing OTC. Data from participants lost to follow-up will be included where possible.

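### The claim of about seven OTC patients per live birth does not follow from its stated inputs and contradicts the planning rate of 0.25 (four per birth, 18 in 72) in the next sentence

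*Protocol article*

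**What the plan says.** All the relevant text is in the protocol article under Sample size calculation. The live birth rate in Turner syndrome is acknowledged to be unknown, so figures are borrowed from cancer survivors: "pregnancy rates following transplantation of thawed ovarian cortical tissue are approximately 50% and live birth rates around 35" per cent. A figure specific to Turner syndrome is added: "Spontaneous miscarriage occurs in an estimated 30–45% of TS pregnancies with autologous oocytes". From these the article concludes: "Based on these figures, approximately seven patients would require OTC for one live birth to occur".

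The next sentence applies a precision formula for a single proportion, with an "expected LBR of 0.25; a confidence interval width of 0.2" and "a significance level (α) of 0.025", and reports that "the required sample size is 72, corresponding to 18 expected live births". The target follows: "We aim to include 100 girls undergoing OTC".

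Two other sections bear on the denominator. Primary outcome counts pregnancies, miscarriages and live births after autotransplantation. Ovarian tissue autotransplantation says that a specialist will first judge whether spontaneous conception, assisted reproduction and/or autotransplantation is the way forward, so not every girl with stored tissue need be transplanted.

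**The concern.** Two adjacent sentences give different expected yields: one birth per seven patients, and one per four. The first is presented as derived from the listed figures, yet those figures do not produce it. The two sentences may also use different denominators, since seven is worded per OTC while the borrowed rates are per transplantation, but no link between the two is given.

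This paragraph is the study's only quantitative justification. A reader cannot tell whether 100 procedures are expected to yield 100 × 0.25 = 25 births, the 18 tied to the required sample size, or about 14. If the difference between seven and four reflects girls who never return for transplantation, the target of 100 OTCs does not supply the 72 women that the calculation requires.

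**Working it through.** **Inputs** (all from Sample size calculation): pregnancy rate 0.50; live birth rate 0.35; miscarriage in Turner syndrome 0.30–0.45; seven patients per birth; planning rate p = 0.25; interval width W = 0.20; α = 0.025, sidedness not stated; required n = 72; expected births 18; target 100 OTCs.

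**Step 1: the plan's own n.** The formula is n = 4z²p(1 − p)/W².
- With 0.025 in each tail, z = 1.96: n = 4 × 3.8416 × 0.1875 / 0.04 = 72.03. This reproduces 72.
- Expected births: 72 × 0.25 = 18. This also reproduces.
- With 0.025 as the two-sided total, z = 2.241: n = 94.2, so 95. This does not reproduce 72.

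So 0.25, 0.20, 72 and 18 agree with one another when α is the area of each tail.

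**Step 2: patients per birth from the listed inputs.**

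| Combination | Live birth rate | Patients per birth |
|---|---|---|
| 0.50 × (1 − 0.30) | 0.350 | 2.9 |
| 0.50 × (1 − 0.45) | 0.275 | 3.6 |
| 0.35 × (1 − 0.30) | 0.245 | 4.1 |
| 0.35 × (1 − 0.45) | 0.193 | 5.2 |
| Planning rate 0.25 | 0.250 | 4.0 |
| Stated: seven | 0.143 | 7.0 |

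Reading 35% as live births per pregnancy does not help: 0.50 × 0.35 = 0.175, or 5.7 per birth, and deducting miscarriage in Turner syndrome as well gives 8.2 to 10.4. A value near seven appears from 0.50 × 0.30 = 0.15 (6.7), but that product is pregnancies lost, not births.

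**Step 3: size of the conflict.** At one in seven, 72 women give 72/7 = 10.3 births instead of 18, which is 43% fewer.

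**Step 4: can different denominators reconcile the two figures?** Suppose seven is per OTC and four is per transplantation.
- Implied return rate: 4/7 = 0.57.
- 100 OTCs then give 57 transplanted women and 57.1 × 0.25 = 14.3 births.
- The 95% interval width at n = 57 is 2 × 1.96 × √(0.1875/57) = 0.22.
- Reaching 72 transplanted women would take 72/0.571 = 126 OTCs.

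If instead the margin from 72 to 100 is meant to cover non-return, the implied return rate is 72%. That gives 100/18 = 5.6 OTCs per birth, again not seven.

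**The case against.** The strongest reply is that seven does not enter the formula. The rate of 0.25, the width, 72 and 18 are coherent without it, and a true rate of 1/7 would lower the n needed for width 0.20 to about 48 (47.04 before rounding up). This stands: neither the 72 nor the target of 100 was computed from seven. It does not remove the contradiction in expected yield. The different-denominator explanation also fails as the text stands, because the sentence claims to rest on the listed figures and those include no return rate.

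Four stronger readings are tempting, and the article does not support them.

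- *That α = 0.025 cannot give 72.* It does when taken as the area of each tail. Only the sidedness is unstated. Read as a two-sided total it would give 95, and a width of 0.229 at n = 72. The target of 100 exceeds both 72 and 95, so this is a wording matter.
- *That 0.25 counts miscarriage twice.* The nearest product, 0.35 × 0.70 = 0.245, might do so if the 50% and 35% share a denominator. The article does not say how 0.25 was obtained, and it may be a rounded or cautious value.
- *That the planned precision is undefined.* Step 1 shows otherwise.
- *That families are counselled with these figures.* The counselling content listed under Assessment of ovarian function covers success in other patient groups and earlier experience in Turner syndrome. It mentions neither seven nor 0.25.

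**Conclusion.** The point holds for the sentence on seven patients. It is not derivable from the inputs it cites (2.9 to 5.2 by natural combinations) and conflicts with the planning rate beside it (four per birth). The expected yield differs by a factor of 7/4 = 1.75, or about 10 against 18 births in 72 women.

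The consequence depends on what was meant. If seven is simply an error, the calculation is otherwise sound and the correction is editorial. If seven reflects incomplete return for transplantation, 100 OTCs fall short of the stated 72 women, 18 births and width of 0.20, giving about 57, 14 and 0.22. The 57% is inferred here from 4/7 and is an assumption. The article gives no return rate, so the sponsor must say which case applies.

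**What to change.** Rewrite the paragraph around one expected live birth rate. State its denominator (per OTC or per transplantation) and how it was derived from the cited inputs. Then take one of two routes.

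1. Delete the figure of seven, or replace it with four per transplantation, in line with 18 births in 72 transplanted women.
2. Keep seven per OTC, state the return-rate assumption behind it, and restate the number of transplanted women, expected births and interval width that 100 OTCs deliver.

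As a minor clarification, describe the interval as a 95% confidence interval (0.025 per tail) in place of the bare significance level.

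The first route costs a few sentences and no participants. The second also costs only text if the sponsor accepts the lower yield and wider interval; holding to 72 transplanted women at a 57% return rate would take about 126 OTCs.

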**Objective:**

To investigate long-term reproductive outcomes following OTC in girls with TS.

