### Study period

Recruitment began in January 2024, and the study is expected to continue until 2050.

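### The required 72 are transplanted women but the target is 100 girls at OTC, with no stated link, so the planned precision holds only if at least 72% are transplanted and followed

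*Protocol article*

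**What the plan says.** All references are to the Protocol article.

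- **Sample size calculation, source of the rates.** Among female cancer survivors, "pregnancy rates following transplantation of thawed ovarian cortical tissue are approximately 50% and live birth rates around 35" per cent. For Turner syndrome the section adds: "Spontaneous miscarriage occurs in an estimated 30–45% of TS pregnancies with autologous oocytes". From these it concludes that about seven patients must undergo OTC for one live birth.
- **Sample size calculation, precision.** The inputs are "expected LBR of 0.25; a confidence interval width of 0.2; and a significance level (α) of 0.025", and the result is that "the required sample size is 72, corresponding to 18 expected live births".
- **Sample size calculation, target.** "We aim to include 100 girls undergoing OTC". No transplanted fraction and no loss rate is given. The section says only that data from girls lost to follow-up will be used where possible.
- **Primary outcome.** "Number of pregnancies, miscarriages, and live births in women with TS following autotransplantation of cryopreserved and thawed ovarian cortical tissue". The Statistical analysis section describes the same events, also after autotransplantation.
- **Abstract, Objective.** "To investigate long-term reproductive outcomes following OTC in girls with TS". The Background words the aim more narrowly, as OTC in childhood followed by autotransplantation in adulthood.
- **Ovarian tissue autotransplantation.** Transplantation takes place only if indicated, after a specialist has weighed spontaneous conception and assisted reproduction.
- **Timing.** Entry age is 2 to 17 years, recruitment began in January 2024, and "the study is expected to continue until 2050".

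**The concern.** The calculation and the target count different people. A rate observed after transplantation, applied to an outcome counted after transplantation, gives a required number of transplanted women. The recruitment target counts girls at oophorectomy, years before anyone knows whether the tissue will be used. Some will not want it, some will conceive without it, and some may still be young when follow-up is expected to end. A girl who entered aged 2 in 2024 is 28 in 2050, and one who entered later at that age is younger still.

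Two things are at stake. First, a reader will take 100 OTCs to deliver an interval 0.2 wide and about 18 live births, which depends on an unstated fraction. Second, the abstract's Conclusion promises evidence for counselling girls and families. A family deciding on oophorectomy needs the chance of a live birth per girl who has OTC, which is lower than the chance per transplanted woman unless every girl is transplanted. The section places a per-OTC figure (one in seven) beside a rate of 0.25 without naming the unit of either.

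**Working it through.** **1. Reproduce the plan's figure.** Inputs from the Sample size calculation: p = 0.25 and total width W = 0.20. For a single proportion, n = 4 z² p(1 − p) / W². With z = 1.96:

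n = 4 × 3.8416 × 0.1875 / 0.04 = 72.03, and 72 × 0.25 = 18 live births.

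Both stated figures reproduce. The stated α of 0.025 must be read as per tail, that is, a two-sided 95% interval. Read as a two-sided level it gives 94.2.

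**2. Which unit is 72?** The section does not say, so this is an inference from three facts.

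- The 50% and 35% source rates are described as following transplantation.
- The primary outcome and its analysis count only events after autotransplantation.
- If 0.25 were per OTC, one live birth would need 1/0.25 = 4 patients. The same section says about seven, which is 1/7 = 0.143.

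So 72 is most sensibly a number of transplanted women.

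**3. What 100 OTCs then deliver.** The fraction needed is 72/100 = 72%, transplanted and followed. For a transplanted fraction f, n = 100f, the Wald 95% width is 2 × 1.96 × √(0.1875/n), and expected live births are 0.25n. The documents give no f, so apart from the 72% needed and the 100% upper limit, the values below are assumptions.

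| f | Transplanted | 95% CI width | Expected live births | OTCs needed for 72 transplanted |
|---|---|---|---|---|
| 100% | 100 | 0.170 | 25 | 72 |
| 72% | 72 | 0.200 | 18 | 100 |
| 50% | 50 | 0.240 | 12.5 | 144 |
| 40% | 40 | 0.268 | 10 | 180 |
| 30% | 30 | 0.310 | 7.5 | 240 |

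**4. Can one in seven be obtained from the cited rates?** Applying the 30–45% miscarriage range to the 35% live birth rate gives 0.35 × 0.55 = 0.193 to 0.35 × 0.70 = 0.245, or one in 5.2 to one in 4.1. Applying it to the 50% pregnancy rate gives 0.50 × 0.55 = 0.275 to 0.50 × 0.70 = 0.35, or one in 3.6 to one in 2.9. Neither route reaches seven. The article shows no derivation, so 0.143 and 0.25 stand side by side unreconciled.

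**The case against.** The strongest reply has four parts.

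- **The gap from 72 to 100 is an attrition allowance.** The target is followed directly by the sentence on loss to follow-up, and a condensed article may leave the figure to the full protocol. This is possible. However, the article states no allowance, and non-transplantation is a different and probably larger source of shortfall than loss to follow-up.
- **The study is exploratory and descriptive.** No hypothesis test is planned, and at 50 transplanted women the half-width moves only from 0.10 to 0.12. This stands and limits the severity. Marked loss needs fractions of about 30–40%, which the documents neither give nor exclude.
- **A per-transplant result is a legitimate primary question.** The Background ties the aim to later autotransplantation and reports only three documented cases in Turner syndrome. This also stands. A reader might infer that the primary outcome cannot answer the abstract's objective, but that goes too far. The outcome is a count with no fixed denominator, and births after transplantation can also be divided by all girls who had OTC. Making a per-OTC rate co-primary would be a design preference.
- **One in seven and 0.25 do not define a transplanted fraction.** A reader might divide 0.143 by 0.25 and conclude that the plan expects 57% to be transplanted, or that its own per-OTC expectation is a reliable 14%. The documents do not support this. The section bases seven on pregnancy, live birth and miscarriage rates, none of which is a transplanted fraction. Another route, such as 0.25 × 0.55 = 0.1375 (one in 7.3), comes close without one.

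**Conclusion.** The point holds as a mismatch of units. The number 72 is correctly calculated but refers, by inference from its source rates and the primary outcome, to transplanted women. The target of 100 refers to girls at OTC. The width of 0.2 and the 18 live births therefore require at least 72% transplanted and followed, a condition that the article neither states nor justifies. With assumed fractions of 50%, 40% and 30%, the width is 0.24, 0.27 and 0.31, with 12.5, 10 and 7.5 expected live births. Separately, about seven OTC patients per live birth and a rate of 0.25 are not reconciled.

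These figures assume a true per-transplant rate of 0.25, one binary outcome per woman and a Wald interval. A reader might go further and estimate how many women will be too young for transplantation in 2050. The article gives no recruitment end, no age distribution and no age at transplantation, and calls 2050 only expected, so such shares would rest on assumptions. The point should be fixed, but it does not invalidate the study.

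**What to change.** **(a) Sample size section.** State that 72 and 0.25 refer to transplanted women. Give the assumed fraction of OTC girls who will be transplanted and followed, with its basis. Show the interval width and expected live births over a range of fractions, as in the table above. Reconcile the one-in-seven figure with 0.25 and name the unit of each.

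**(b) Secondary analysis.** Beside the per-transplant result, report live birth among all girls who had OTC. Keep never-transplanted women in the denominator and tabulate the reasons. Show births after transplantation separately from births by other conception, so that the graft's contribution stays visible. Use a cumulative incidence by age with a 95% confidence interval, because women still young when follow-up ends will be censored. For the same reason, do not quote a simple binomial width for 100 girls as its precision.

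**Cost.** A change of wording and one extra analysis, which should use data from the follow-up already planned. No change to treatment or recruitment is needed. The downside is that the per-OTC rate after transplantation will be lower than the per-transplant rate, so the headline will look less favourable.
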